#### **3.8.2 Dose escalation and dose-limiting toxicity**

The single dose-escalation scheme, denoted as S-1, will be as follows 3+3: cohort 1 ( $5.0 \times 10^7$  cells), cohort 2 ( $1.0 \times 10^8$  cells), cohort 3 ( $1.5 \times 10^8$  cells) and cohort 4 ( $2.0 \times 10^8$  cells). Each patient will be observed for 3days for signs of dose-limiting toxicity (DLT) before another patient in the same cohort can receive treatment. The last patient of each cohort will be observed for 7days before the next cohort with a higher dose can start to receive treatment. The first three patients in a cohort will be observed to determine the next action. If one of the three patients shows signs of DLT, the next three patients in the cohort will be treated with the same dose. If two or more patients in any cohort show signs of DLT, then the study will be concluded. The study will only proceed to the next cohort if none of the first three patients shows signs of DLT after the outlined observation periods have elapsed or if only one out of the six patients in a cohort shows signs of DLT. The specific rules for dose escalation can be found in figure1.

The first dose of UC-MSCs in cohort 1 (three patients initially) will be  $5.0 \times 10^7$  cells. The maximum-tolerated dose (MTD) is determined as the highest dose that induces DLT in no more than one patient among the extended cohort of six patients. Patients will be recruited into four cohorts and will begin dosing at successively higher doses until the MTD is established or up to a dosage of  $2.0 \times 10^8$  cells.

[figure not shown]

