| Recruitment status | Participants in all dose groups have completed 28 days of observation after the first dose, and 2-year safety follow-up is ongoing. The trial finishing date is estimated as March 25, 2026                                                                                                                                                                                                                                                                                                                                                                                                                                                                                                                                                                                                                                                                                                                                                                                                                                                                                                                                                            |
| Primary outcomes   | The primary outcomes are the incidence of DLTs, adverse events (AEs), MTD and the change in the MELD score from baseline to the 28th day after the first dose intervention                                                                                                                                                                                                                                                                                                                                                                                                                                                                                                                                                                                                                                                                                                                                                                                                                                                                                                                                                                             |

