## **3.4 Outcomes**

### **3.4.1 Primary outcomes**

The primary outcomes are the incidence of DLTs, adverse events(AEs), MTD and the change in the MELD score from baseline to the 28th day after the first dose intervention.

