### **3.6 Sample size**

This is a proof-of-concept study. A total of 3-6 patients will be recruited for each dose cohort, comprising low and high dose groups, with 3 patients in each cohort initially. The additional patients will be added to the cohort if dose-limiting toxicity is presented. A total of 6-12 patients will be recruited for the study [19].

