#### **3.8.2 Dose escalation and dose-limiting toxicity**

In this study, a total of two dose groups ( $1.0 \times 10^8$  cells,  $2.0 \times 10^8$  cells) were set up, multiple dose escalation was performed according to the "3+3" rule, each subject was only entered into one corresponding dose group. Starting from the low-dose group ( $1.0 \times 10^8$  cells), each subject was closely observed for 7 days after the corresponding dose of UC-MSCs treatment, and the possible DLTs were evaluated. Subjects in the same dose group must complete the DLT assessment for 7 days before starting the next subject, and the first patient in the high-dose group ( $2.0 \times 10^8$  cells) could not be enrolled until the last patient in the low-dose group ( $1.0 \times 10^8$  cells) had completed a 28-day safety assessment. During dose escalation, safety data from the previous dose group were used by the investigator and the sponsor to determine whether to proceed with the next dose.

During the observation period of DLT, if none of the 3 subjects in a dose group observed DLT (0/3), they could be escalated to the next dose group. If there was one DLT (1/3) in a dose group, 3

additional subjects in this dose group were required, and if the 3 additional subjects had no DLT (total DLT 1/6), they could escalate to the next dose group. If one or more DLTs (total DLTs  $\geq 2/6$ ) occurred in the supplementary 3 patients, the dose escalation was terminated, and the previous dosage was MTD. If no DLT occurred after the completion of dose escalation in either dose group, the decision to continue dose escalation was made in joint discussion between the investigator and the sponsor. The specific rules for dose escalation can be found in **Figure 1** [19].

[figure not shown]

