**Figure 1 Dose escalation flowchart**

### 3.8.3 Assessment of DLT and MTD

DLT will be evaluated according to the National Cancer Institute Common Toxicity Criteria (NCI-CTC) 5.0 ([https://ctep.cancer.gov/protocoldevelopment/electronic\\_applications/ctc.htm](https://ctep.cancer.gov/protocoldevelopment/electronic_applications/ctc.htm)). The following drug-related adverse events were considered DLTs: (1) Grade  $\geq 3$  allergic reactions related to UC-MSCs, such as dyspnea, chills and fever; (2) Grade  $\geq 3$  embolic adverse events related to UC-MSCs, such as acute pulmonary embolism, deep vein thrombosis, etc.; (3) Grade  $\geq 3$  hematological toxicity related to UC-MSCs; (4) Any unexpected toxicity requiring discontinuation of treatment at the discretion of the investigator and sponsor.

During the observation period of DLT, if none of the 3 subjects in a dose group observed DLT (0/3), they could be escalated to the next dose group. If there was one DLT (1/3) in a dose group, 3 additional subjects in this dose group were required, and if the 3 additional subjects had no DLT (total DLT 1/6), they could escalate to the next dose group. If one or more DLTs (total DLTs  $\geq 2/6$ )

occurred in the supplementary 3 patients, the dose escalation was terminated, and the previous dosage was MTD. If no DLT occurred after the completion of dose escalation in either dose group, the decision to continue dose escalation was made in joint discussion between the investigator and the sponsor.

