## **3.10 Statistical considerations**

### **3.10.1 Statistical methods**

Efficacy will be assessed according to the intent-to-treat (ITT) analysis principle, while safety will be assessed by analyzing adverse events within the cohorts and noting their category and severity. Continuous variables will be expressed as the mean with the standard deviation (SD). Categorical variables will be expressed as a number count together with the rate or composition ratio. The chi-square test or Fisher's exact test will be used to compare categorical variables between different doses used by the cohorts for evaluating efficacy. They will also be used to compare the rate of adverse events occurrence between cohorts to assess safety. The change in the patients' lab values in each cohort after treatment will also be described to explore any potential correlations between these changes and the occurrence of adverse events. Continuous variables will be

compared using the *t*-test. However, comparisons will be made using the Wilcoxon signed-rank test when analyzing changes in continuous quantitative variables before and after treatment. The 95% confidence interval (95% CI) will be calculated for the outcomes of the continuous variables. A more detailed plan for the statistical analysis will be formulated and finalized before the data gathering is finished for the study. This final plan will dictate the method and content of the study's statistical analysis.  $P < 0.05$  will be considered as showing statistical significance. All the statistical analyses will be performed using SAS 9.4 (Statistics Analysis System, Inc. Cary, NC, USA).

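### The MSC-DLC-1b text lets 1.0×10^8 cells be named the MTD, a primary outcome, on 0/3 with no confirmation in six patients, and gives no usable answer if that first dose group fails

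*Supplement*

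**What the plan says.** All references are to the MSC-DLC-1b protocol unless 1a is named.

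- **Primary outcome (3.4.1).** "The primary outcomes are the incidence of DLTs, adverse events(AEs), MTD" and the day-28 change in MELD score. The MTD is therefore a primary result.
- **Passing a dose (3.8.2).** During DLT observation, "if none of the 3 subjects in a dose group observed DLT (0/3), they could be escalated to the next dose group". With one DLT in three, three more patients are treated, and 1/6 also passes.
- **Naming the MTD (3.8.2 and 3.8.3).** If one or more further DLTs, at least two of six in all, "occurred in the supplementary 3 patients, the dose escalation was terminated, and the previous dosage was MTD" (3.8.2). Section 3.8.3 repeats that "the dose escalation was terminated, and the previous dosage was MTD". No other sentence in either section names an MTD.
- **Cohort size (3.6).** Each of the two dose groups starts with three patients and may have up to six, for a total of 6–12. "The additional patients will be added to the cohort if dose-limiting toxicity is presented". No other reason for expansion is given.
- **Figure 1.** Section 3.8.2 sends the reader to this flowchart for the specific escalation rules. It is not reproduced in the text available.
- **Status (section 1).** "Participants in all dose groups have completed 28 days of observation after the first dose".

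**The concern.** Escalating on 0/3 is ordinary 3+3 practice and is not in dispute. The difficulty comes when the trial has to step back. The lower dose was passed only as a gate to the next one, yet when the higher dose fails it becomes the MTD without any further patient. The label then suggests an established dose for a three-infusion course, while the data behind it may be three patients without a DLT.

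The same sentence fails at the other end. Only 1.0×10^8 and 2.0×10^8 cells are tested, so at least two of six at 1.0×10^8 makes the previous dose one that does not exist in 1b. A primary outcome should have a defined value, or a defined statement that there is none, on every path the rule describes.

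**Working it through.** **Inputs.** From the protocol: two doses, three patients initially and at most six per dose, passing on 0/3 or 1/6, and the MTD rule at two or more of six. The documents give no DLT rates, so those below are assumptions.

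**1. The plan's own figure.** 2 × 3 = 6 and 2 × 6 = 12, which reproduces the stated 6–12.

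**2. The path.** Low dose 0/3, so escalate. High dose 1/3, so add three. At least one DLT among those three, so stop. The MTD is 1.0×10^8 cells on three patients, with 3 + 6 = 9 treated in all.

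**3. What 0/3 supports.** The exact two-sided 95% upper limit after 0/n is 1 − 0.025^(1/n).
- 0/3: 1 − 0.025^(1/3) = 0.708
- 0/6: 1 − 0.025^(1/6) = 0.459
- 1/6: 0.641 (Clopper-Pearson)

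A dose with a true DLT rate of 30% gives 0/3 with probability 0.7³ = 0.343.

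**4. How often the path occurs.** For DLT rate p, let q0 = (1−p)³ and q1 = 3p(1−p)². Then pass = q0 + q1·q0, and the written failure branch is fail6 = q1·(1−q0). The MTD is named at the low dose with probability pass(low) × fail6(high), and on three patients with probability q0(low) × fail6(high).

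At 10% (low) and 30% (high):
- q0(low) = 0.729, q1(low) = 0.243, pass(low) = 0.729 + 0.243 × 0.729 = 0.906
- fail6(high) = 0.441 × (1 − 0.343) = 0.290
- Named at all: 0.906 × 0.290 = 0.26. On three patients: 0.729 × 0.290 = 0.21. On six (low dose 1/6): 0.177 × 0.290 = 0.05.

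| Assumed rate, low/high | Low dose named MTD | of which on 0/3 | of which on 1/6 |
|---|---|---|---|
| 5% / 5% | 0.019 | 0.017 | 0.002 |
| 10% / 10% | 0.060 | 0.048 | 0.012 |
| 20% / 20% | 0.133 | 0.096 | 0.037 |
| 10% / 30% | 0.26 | 0.21 | 0.05 |

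Given that the rule names 1.0×10^8, the share resting on three patients is q0/pass = 1/(1 + q1(low)): 88%, 80% and 72% at low-dose rates of 5%, 10% and 20%, whatever the high-dose rate.

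**5. Failure of the first group.** The written branch is reached at 1.0×10^8 with probability fail6(low) = 0.019, 0.066 and 0.187 at rates of 5%, 10% and 20%. In each case the rule points to no dose in 1b.

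**6. Effect of a six-patient condition at 10%/30%.** Without expansion only the 1/6 path still names 1.0×10^8, so the probability falls from 0.26 to 0.05. With the low dose filled to six, it is named if at most one further DLT occurs: [0.729 × (0.729 + 0.243) + 0.177] × 0.290 = 0.886 × 0.290 = 0.26, almost unchanged. The total is then 6 + 6 = 12, the planned ceiling.

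**The case against.** **Figure 1 may hold the missing step.** This stands as a limit. An instruction to fill the lower dose to six would sit naturally in a flowchart. Against it, 3.8.3 repeats the rule without such a step and 3.6 ties added patients to a DLT. If the figure has the step, the prose should match it.

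**The path is uncommon.** At equal rates of 5% to 20% it occurs in about 2% to 10% of trials, and 21% needs the assumed 10%/30% pair. The 72% to 88% shares apply only once the rule has named the low dose. This stands, and it limits the size of the point.

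**Six patients add little.** The upper limit after 1/6 is 64%, against 71% after 0/3. Going from three to six would reverse acceptance (0/3, then at least two of three) in 2%, 5%, 7% and 8% of trials at true rates of 10%, 20%, 30% and 40%. The gain is modest if the six include a DLT and larger if they do not (46%).

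**Changing the definition now is post hoc.** On schedule the last infusion is on day 14 (2.3) and DLT observation lasts seven days (3.8.2), so with 28 days complete in all groups the DLT data are in. In an open-label trial this alters a primary outcome after the fact, and 4.2 requires an approved amendment. This stands and is a real cost.

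**Stronger readings that a reader might infer.** The documents do not support these:
- *That there is no minimum at all.* The cohort rule gives a floor of three. What is missing is confirmation in six.
- *That 1b dropped a working safeguard from 1a.* The 1a protocol (3.8.2) does define the MTD as "the highest dose that induces DLT in no more than one patient among the extended cohort of six patients", but its own 3.6 and 3.8.3 add patients only after a DLT and fall back to the previous dose in the same way.
- *That a DLT-free trial names 2.0×10^8 the MTD on three patients.* The text names no MTD there and leaves further escalation to the investigator and the sponsor.
- *That omitting an interval for the DLT rate is a separate fault.* Section 3.10.1 says "The 95% confidence interval (95% CI) will be calculated for the outcomes of the continuous variables", plans counts with rates for categorical variables, and leaves detail to a later analysis plan. The count 0/3 would be visible.
- *That 2/3 or 3/3 at the high dose also names the low dose.* The 1b text gives no rule for those results, so they are left out above.

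**Conclusion.** The point holds as a defect of the written rule. The only sentence in 1b that names an MTD accepts a dose passed on 0/3, and it has no valid referent when the first group fails. This should be corrected because it decides what may be concluded on a primary outcome, but it is not a threat to the trial as a whole. A floor of three patients exists, and the path is uncommon unless the higher dose is appreciably more toxic. The probabilities rest on assumed DLT rates, on independent patients and on the written two-or-more-of-six branch alone. The existence of the gap does not depend on those rates, but it does depend on Figure 1 adding no expansion step. The documents report no DLT results, so nothing here says that an MTD was in fact named on three patients.

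**What to change.** In 3.8.2 and 3.8.3 of the 1b protocol, state that:

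1. A dose is named MTD only if six patients have been treated there with at most one DLT.
2. When 2.0×10^8 fails and 1.0×10^8 was passed on 0/3, the lower dose is filled to six before any MTD is named.
3. If 1.0×10^8 fails, no MTD is named in 1b.

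Check that Figure 1 agrees.

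If dosing is already over, make no expansion. Report a dose supported by only three patients as the highest dose that met the escalation rule, or as the highest dose tested, with its DLT count and without the MTD label. Document this as an amendment made after the DLT data were available.

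**Cost.** With expansion, up to three more patients, still within 3–6 per group and 6–12 in all, and the time to observe them. Without expansion, fewer trials name an MTD: at 10%/30%, 5% instead of 26% for 1.0×10^8. In either case a formal amendment under 4.2 is needed, and a late one must be declared as such.

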**Figure 1 Dose escalation flowchart**

### 3.8.3 Assessment of DLT and MTD

DLT will be evaluated according to the National Cancer Institute Common Toxicity Criteria (NCI-CTC) 5.0 ([https://ctep.cancer.gov/protocoldevelopment/electronic\\_applications/ctc.htm](https://ctep.cancer.gov/protocoldevelopment/electronic_applications/ctc.htm)). The following drug-related adverse events were considered DLTs: (1) Grade  $\geq 3$  allergic reactions related to UC-MSCs, such as dyspnea, chills and fever; (2) Grade  $\geq 3$  embolic adverse events related to UC-MSCs, such as acute pulmonary embolism, deep vein thrombosis, etc.; (3) Grade  $\geq 3$  hematological toxicity related to UC-MSCs; (4) Any unexpected toxicity requiring discontinuation of treatment at the discretion of the investigator and sponsor.

During the observation period of DLT, if none of the 3 subjects in a dose group observed DLT (0/3), they could be escalated to the next dose group. If there was one DLT (1/3) in a dose group, 3 additional subjects in this dose group were required, and if the 3 additional subjects had no DLT (total DLT 1/6), they could escalate to the next dose group. If one or more DLTs (total DLTs  $\geq 2/6$ )

occurred in the supplementary 3 patients, the dose escalation was terminated, and the previous dosage was MTD. If no DLT occurred after the completion of dose escalation in either dose group, the decision to continue dose escalation was made in joint discussion between the investigator and the sponsor.

### **3.8.4 Product management**

The investigator will designate a dedicated person to be responsible for the storage, distribution, recovery, inventory and recording of investigational drugs. When the investigational product arrive at the research center, the researcher or his authorized person needs to check the storage conditions of the study drugs when they arrive, count the quantity, check the product number, and sign and confirm on the handover record form. The investigator or his authorized person will distribute the investigational drugs, and corresponding records will be kept for each distribution and use.

## **3.9 Data collection and data management**

This study will use an electronic data collection system (EDC) to collect and manage research data to ensure the traceability of clinical trial data; the data management process must comply with GCP specifications and the "Stem Cell Clinical Research Management Measures" (2015 edition) to ensure the authenticity, completeness and accuracy of clinical trial data.

## **3.10 Statistical considerations**

### **3.10.1 Statistical methods**

Efficacy will be assessed according to the intent-to-treat (ITT) analysis principle, while safety will be assessed by analyzing adverse events within the cohorts and noting their category and severity. Continuous variables will be expressed as the mean with the standard deviation (SD). Categorical variables will be expressed as a number count together with the rate or composition ratio. The chi-square test or Fisher's exact test will be used to compare categorical variables between different doses used by the cohorts for evaluating efficacy. They will also be used to compare the rate of adverse events occurrence between cohorts to assess safety. The change in the patients' lab values in each cohort after treatment will also be described to explore any potential correlations between these changes and the occurrence of adverse events. Continuous variables will be

compared using the *t*-test. However, comparisons will be made using the Wilcoxon signed-rank test when analyzing changes in continuous quantitative variables before and after treatment. The 95% confidence interval (95% CI) will be calculated for the outcomes of the continuous variables. A more detailed plan for the statistical analysis will be formulated and finalized before the data gathering is finished for the study. This final plan will dictate the method and content of the study's statistical analysis.  $P < 0.05$  will be considered as showing statistical significance. All the statistical analyses will be performed using SAS 9.4 (Statistics Analysis System, Inc. Cary, NC, USA).

### 3.10.2 Analysis population

**Full Analysis Set(FAS):** According to the principle of Intention to Treat (ITT) will constitute the Full Analysis Set for all subjects who were successfully enrolled and had at least one documented treatment.

**Per Protocol Set(PPS):** It is a subset of FAS subjects who meet the inclusion criteria, not meet the exclusion criteria, complete the treatment regimen, fully adhere to the trial protocol, and not have any major protocol violations (subjects who will discontinue trial treatment due to disease progression will be included in the Per-Protocol Set, PPS).

**Safety Set(SS):** Includes all subjects who have received an infusion. The safety population will primarily be used for the analysis of safety data.

### 3.11 Safety/harms

Adverse events (AEs) and severer adverse events (SAEs) will be monitored and recorded from the time the subject signed informed consent to the completion of the follow-ups. AEs/SAEs will be recorded in detail, including onset date, duration, severity, treatment, relation to the investigational medical product. All AEs/SAEs will be followed up until finalized (recover/relief, stable, deaths, or other explainable circumstances, e.g., lost to follow-up).

SAEs, once identified, must be taken into action and reported within 24 hours. SAEs will be reported to IRB as soon as possible.

